### Analysis plan

The analyses of study data will be performed using the principle of intention-to-treat for the analysis of randomized controlled trials. The exploratory data analysis will be performed for all descriptive statistics, such as means, proportions, variances, and correlation by time and group. Two group (control and intervention) comparison analysis at each time point, across all time points and within each cluster will be performed. One-way crossover design analysis methods will be used for stepped wedge design data, that is, analyses will be performed accounting for potential within-cluster correlation using a random effect model, multilevel model, or generalized estimating equations. Based on each month of the study, we will compare the neonatal mortality rate in those centers that have not yet received the intervention with those in the centers that have. The study hypothesis will be tested on the significance level of alpha = 5 % throughout the analysis. All analyses, summaries, listing, and graphing will be performed on the data, using SAS software (version 9.1 or higher in a Windows environment SAS Institute Inc. Cary, North Carolina, USA). In order to avoid the potential problem of multiple comparisons related to the primary outcomes we plan to apply a Bonferroni correction.

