### Trial design

The health center functions as the unit of allocation, with health centers randomized to an intervention start date using a stepped wedge design. The design is principally a matched one, with before and after comparisons for each unit of randomization. On the hypothesis that 16 health centers are recruited, one health center will be assigned to start each month, and randomization will be stratified in order to ensure balance across time points. In this design, all clusters (health centers) receive the intervention in due course (unidirectional crossover) and, in particular, the intervention is never removed once it has been implemented, which allows convenience and alleviates ethical concerns. All cases will be used in the primary analysis, constituting an intent-to-treat approach. Full study enrollment will be completed at 16 months and duration of participation in the intervention will vary based on randomization assignment, with all clusters enrolled with a unidirectional approach and participating for the last six months of the trial.

All health centers in the trial will be included in the intervention, but will be randomized to one of 16 start dates. The center-level intervention will be implemented one stage at a time, progressively over the study period, until all centers have received the intervention. In addition to center level, patient-level data will also be collected. Thus the analysis is divided into center level and patient level, with the patient-level analysis as the primary outcome. All live births occurring in the study area will be eligible, and pregnant women in the last trimester will be recruited from health center catchment areas using the stepped wedge design, where each area will serve initially as control and later as intervention. The study will enroll a target sample size of 1,957 recently delivered women.

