### Sample size and power calculation(s)

Using all-cause newborn mortality as the exploratory outcome and a stepped wedge design for cluster randomized trials, we would require a total sample size of 1,957, based on 80 % power, a 5 % significance level, and a 10 % rate of loss-to-follow-up, to detect a 20 % reduction in neonatal mortality with a baseline of up to 40 deaths per 1,000 live births at the provincial level. For this study, health centers with an expected minimum of 20 births per month will be included, resulting in a study population of at least 320 per month, or 5,540 participants over one year and five months. This will allow us to meet more than 80 % power of the study primary objectives. Secondary analyses will examine the impact through process indicators based on a smaller sample. Other intervention phase outcomes with higher baseline rates than all-cause mortality (incidence of newborns with specific danger signs and proportion of newborns with danger signs referred to an appropriate facility) are hypothesized to demonstrate 20 % or greater improved outcome in the intervention group, but the lack of reliable baseline data on these does not allow us to use them for power calculations.

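### The article lists time-confounded and same-month comparisons without saying which decides the six primary outcomes, calls the design principally before-after, and names no calendar-time adjustment

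*Protocol article*

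**What the plan says.** All places are in the protocol article.

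- **Trial design** characterises the comparison: "The design is principally a matched one, with before and after comparisons for each unit of randomization". Crossover is one-way, the intervention is never withdrawn, and on the assumption of 16 centres "one health center will be assigned to start each month, and randomization will be stratified in order to ensure balance across time points".
- **Analysis plan** lists the comparisons: "Two group (control and intervention) comparison analysis at each time point, across all time points and within each cluster will be performed". It then names one-way crossover methods and explains them as analyses "accounting for potential within-cluster correlation using a random effect model, multilevel model, or generalized estimating equations".
- **Analysis plan** also commits to a same-month contrast for one endpoint: "Based on each month of the study, we will compare the neonatal mortality rate in those centers that have not yet received the intervention", set against the centres that have. Under Outcomes, mortality is exploratory.
- **Outcomes** lists six primary outcomes: danger-sign knowledge in mothers and in volunteers, care-seeking, time to referral, and hand washing by families and by health center staff. No section says which of the listed comparisons gives the deciding estimate for them.
- No section names a month, period or calendar-time effect.

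**The concern.** In a one-way roll-out, every centre's intervention months come after its control months. A before-after difference within a centre, or a comparison pooled over all months, therefore mixes the intervention effect with whatever else changed over time. Allowing for within-cluster correlation does not separate the two. Randomised start dates protect against a common trend only if the analysis compares centres in the same month or models month.

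Drift is plausible here. The Abstract says that initiatives on other causes of newborn illness are under way, and the Background describes a national resolve to intensify newborn work. Knowledge, reported hand washing and care-seeking are what such programmes could move. A favourable drift would be credited to the package and an unfavourable one would mask a benefit. The results are meant to inform policy and scale-up.

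**Working it through.** **Inputs.** From the article: 16 centres, one starting each month (Trial design), and 17 months (Sample size and power calculation(s): "5,540 participants over one year and five months"). Assumed, because the documents give no figure: prevalence 50%, between-centre SD 5 points, linear drift of 2, 5 or 10 points per year, and 7 women per centre-month (16 × 17 × 7 = 1,904, close to the target of 1,957). The plan states no figure for trend bias, so there is none to reproduce.

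**1. Calendar gap.** Let centre s (s = 1 to 16) cross over after month s.
- Control cells: 136, mean month Σ j(17 − j)/136 = 816/136 = 6.0.
- Intervention cells: 136, mean month Σ j(j − 1)/136 = 1632/136 = 12.0.
- Pooled gap: 12.0 − 6.0 = 6.0 months.
- Gap within any centre: (s + 18)/2 − (s + 1)/2 = 8.5 months.

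Trial design also mentions a last six months with all centres participating. If that makes 22 months, the gaps are 9.0 and 11.0. A random-intercept model without month effects weights between the pooled and within-centre contrasts, so its gap lies between 6.0 and 8.5 months in the 17-month layout.

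**2. Bias = drift × gap / 12.**

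| Drift (points/year) | Pooled (6.0 months) | Within centre (8.5 months) |
|---|---|---|
| 2 | 1.0 | 1.4 |
| 5 | 2.5 | 3.5 |
| 10 | 5.0 | 7.1 |

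**3. Type I error with no true effect.** In 2,000 simulated trials per setting, a centre-adjusted model was fitted with and without month effects.

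| Drift | 7 per cell, no month term | 7 per cell, month effects | 20 per cell, no month term |
|---|---|---|---|
| 2 | 8% | 4.9% | 13% |
| 5 | 26% | 4.4% | 58% |
| 10 | 74% | 5.3% | 99% |

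Bias with month effects was about 0, and so was the bias of a weighted same-month comparison. More data makes the unadjusted error worse.

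A closed form agrees. The within-centre sum of squares of the intervention indicator is Σ s(17 − s)/17 = 816/17 = 48. The standard error at 7 per cell is then √(0.25/7/48) = 0.0273. A drift of 5 points per year gives z = 0.0354/0.0273 = 1.30 and P(|Z + 1.30| > 1.96) = 25%. Drifts of 2 and 10 give 8% and 74%.

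**4. Effect of the planned Bonferroni correction.** Assume it divides 5% by six (0.0083, critical value 2.638). The same closed form at 7 per cell gives 1.8%, 9.0% and 48% against the intended 0.83%.

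**5. Trends the Background does give**, carried over 6.0 and 8.5 months as (later/earlier)^(gap/60):
- Neonatal mortality, 28 to 27 per 1,000: 0.996 and 0.995, a spurious fall of 0.4% to 0.5%.
- Under-five mortality, 83 to 54 per 1,000: 0.958 and 0.941, a fall of 4.2% to 5.9%.

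The reduction that the sample size targets is 20%. Neither trend is for a primary outcome.

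**6. Price of month effects.** Removing centre and month means leaves a sum of squares of 136 − 88 − 93.5 + 68 = 22.5. The standard error therefore rises by √(48/22.5) = 1.46. A separate simulation with random-intercept-type weights gave SDs of about 0.025 and 0.035, a ratio of 1.4.

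**The case against.** - **Same-month comparisons are planned.** The sentence listing the comparisons begins with one at each time point, and mortality is compared month by month. Both are free of a common trend. This stands, so a reader who infers that any secular trend will be counted as an intervention effect goes too far. It does not settle the primary outcomes: the explicit monthly commitment is for an exploratory endpoint. With one centre crossing per month, single-month contrasts run from 1 against 15 centres to 15 against 1. Months with all centres on intervention have no concurrent control.
- **The model families can carry month effects, and an article leaves covariates to the analysis plan.** This also stands. The text does not exclude a month term, so a reader cannot conclude that these models would declare success from drift alone. The point rests instead on what is stated: two of the three listed comparisons are time-confounded, the design is labelled before-after, and no analysis is ranked first.
- **"The design is principally a matched one, with before and after comparisons for each unit of randomization" may only describe how centres are observed.** That reading is possible. But the sentence is the article's only statement of the principal comparison, and an analysis plan written from it could inherit the confounding.
- **The drift sizes are assumed.** Correct. At 2 points per year and 7 women per cell the excess error is small. The 7-per-cell setting also does not represent the volunteer and staff outcomes, nor care-seeking and time to referral, which arise only when danger signs occur.
- **Bonferroni lowers the false-positive rates.** It does, but it leaves the bias unchanged, and the rates stay above the intended level.

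**Conclusion.** The concern holds in limited form. The article mixes time-confounded and same-month comparisons, describes the design as principally before-after, names no calendar-time adjustment and does not say which analysis decides the six primary outcomes. The 6.0- and 8.5-month gaps follow from the stated roll-out over 17 months and do not depend on the assumed drift. The harm does depend on it: type I error without a month term ranges from about 8% (2 points per year) to 74% (10 points per year) at about 7 women per cell, under the stated assumptions of 50% prevalence and linear drift. For mortality, the article's neonatal trend gives under 1% bias, so the exposure lies with the knowledge and behaviour outcomes, for which no trend is documented.

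**What to change.** 1. In Analysis plan, state that the primary estimate for each primary outcome comes from one mixed model or GEE with fixed calendar-month effects, a centre effect and the intervention indicator.
2. Label the pooled, within-cluster and single-month comparisons descriptive.
3. In Trial design, reword the sentence on matching so that before-after comparison is not the basis of inference.

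This changes wording only: no design or data-collection change is needed. The cost is precision, with standard errors about 1.4 to 1.5 times those of the analysis without month effects. The smaller unadjusted standard error is valid only if there is no trend, which the documents give no data to support for these outcomes.

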### Outcomes

#### Primary outcomes

The primary outcomes for the study are as follows:Percentage of mothers who know at least three danger signs;Percentage of VHSG volunteers who know six danger signs;Percentage of families who seek care from an appropriate facility;Decreased time between onset of suspected danger signs and referral to appropriate facility;Improved infection prevention behaviors by family, as measured by the proportion of hand washing with soap at key events, calculated as a composite score from the percentage of mothers or caretakers reporting hand washing at the following key events: after going to toilet, before touching newborn, before eating, and after cleaning baby’s bottom;Improved infection prevention and control behavior among health center staff, as measured by the proportion of appropriate hand washing with soap or disinfectant at key points in provision of care to mothers and newborns, calculated as a composite score from: percentage of health center staff reporting hand washing: before patient contact (when they examine mother and newborn), before and after aseptic procedure, after exposure to blood or body fluids, after patient contact (after removing gloves), and after touching patient surroundings.

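### GEE is offered as interchangeable with mixed models at 16 centres; in its ordinary uncorrected form it would not hold the Bonferroni-adjusted level

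*Protocol article*

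**What the plan says.** Under Trial design the number of clusters is fixed: "On the hypothesis that 16 health centers are recruited, one health center will be assigned to start each month", and each centre is randomized to one of 16 start dates. The design is therefore a stepped wedge with 16 sequences of one centre each.

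Under Analysis plan, clustering is to be handled "using a random effect model, multilevel model, or generalized estimating equations". The three are listed side by side with no preference. No variance estimator, reference distribution or degrees of freedom is given, and no small-sample correction is named or excluded.

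On error control the same section says "The study hypothesis will be tested on the significance level of alpha = 5 % throughout the analysis", and for the primary outcomes "we plan to apply a Bonferroni correction". The divisor is not stated. The Primary outcomes section lists six: mothers' knowledge, volunteers' knowledge, care-seeking, time to referral, family hand washing and staff hand washing.

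**The concern.** The sandwich variance of GEE relies on a large number of clusters. With 16 it is biased downward and is itself noisy, so the test statistic has heavier tails than the normal. Both effects grow, relative to the nominal level, further into the tail. A Bonferroni-adjusted test is decided far out in the tail, so a distortion that is tolerable at 5 % becomes a multiple of the level at 0.83 %.

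Two commitments in the Analysis plan section would then pull against each other. One method it permits, used in the form most analysts would reach for first, would not deliver the multiplicity control it promises. The article expects the results to shape national newborn policy, so a false positive on a primary outcome would matter.

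**Working it through.** **Inputs from the article.** 16 centres and 16 start dates (Trial design). Seventeen months of recruitment and at least 20 births per centre-month (Sample size and power calculation(s)). Target of 1,957 women, so 1,957 / (16 × 17) = 7.2 per centre-month. Alpha 5 % with Bonferroni (Analysis plan).

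**Assumed.** Two-sided tests; divisor 6; 7 or 20 women per centre-month; ICC 0.001 to 0.10; binary patient-level outcome with prevalence 0.1 to 0.8.

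**Intended level.** The article gives no GEE error rate to reproduce, so the benchmark is its own nominal level. Per test, 0.05 / 6 = 0.00833, critical z = 2.638. Over six independent tests, 1 − (1 − 0.00833)^6 = 4.9 %.

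**Analytic check.** Let r be the ratio of the mean estimated standard error to the true one, and let the statistic follow t on 15 df rather than a normal. The actual level is then 2 × P(t15 > 2.638 r).

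| r | SE bias only (normal tail) | SE bias and t15 tail |
|---|---|---|
| 1.00 | 0.83 % (×1.0) | 1.86 % (×2.2) |
| 0.95 | 1.22 % (×1.5) | 2.42 % (×2.9) |
| 0.90 | 1.76 % (×2.1) | 3.14 % (×3.8) |
| 0.88 | 2.03 % (×2.4) | 3.47 % (×4.2) |

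Using a normal reference where t15 applies gives 2.2 times nominal by itself. A 10 % shortfall in the standard error gives 2.1 times by itself. Together they give 3.8 times.

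**Simulation under no effect, uncorrected sandwich with normal reference.**

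- Logistic GEE, exchangeable, month as fixed effects, ICC 0.01 to 0.10, 2,000 or 4,000 trials per setting: 8.4 to 10.7 % at nominal 5 %; 2.4 to 3.7 % at nominal 0.83 %.
- Logistic GEE, 42 scenarios of 4,000 to 6,000 trials, varying prevalence, ICC, cell size, month coding and working correlation: 7.6 to 10.7 % at 5 %; 2.2 to 3.6 % at 0.83 % (2.6 to 4.3 times, mostly 3 to 4). With categorical month, 3.1 to 4.3 times. Mean standard error was 0.87 to 0.95 of the true value.
- Identity-link GEE with month effects, ICC 0.01 to 0.10: about 8 to 9 % at 5 %; 2.3 to 2.9 % at 0.83 %.

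The Monte Carlo standard error at a rate of 3 % with 4,000 trials is √(0.03 × 0.97 / 4,000) = 0.27 percentage points, so the ends of these ranges agree. A fair summary is roughly 2.3 to 3.6 %.

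**Alternatives at nominal 0.83 %.**

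- Same uncorrected standard error, t15 reference: 1.0 to 2.5 times nominal.
- Mancl-DeRouen variance with t14: 0.4 to 0.8 % (logistic) and 0.3 to 0.5 % (identity link). With t15, 0.4 to 1.5 times nominal, mostly 0.6 to 1.1.
- Model-based standard error with exchangeable correlation, a proxy for the mixed-model options: about 0.8 to 2.1 times, mostly 1.0 to 1.5.

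**Family error if all six tests ran at rate p and were independent.** 1 − (1 − p)^6 gives 13.6 % at p = 2.4 %, 16.7 % at 3.0 % and 20.2 % at 3.7 %: about 14 to 20 %.

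**The case against.** The strongest reply is that the article never specifies the test simulated here. It names GEE but not an uncorrected sandwich or normal critical values, and a bias-corrected GEE with a t reference fits its wording equally well. Such details usually sit in a statistical analysis plan, which is not shown, so their absence from a journal article is no fault in itself. All of that stands. A reader might infer that the trial's primary tests will run at three to four times their level. The documents do not support that: GEE is one of three options, and the inflated form is one way of carrying it out.

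A reader might also blame the standard errors alone, or apply the figure to every primary outcome. Neither is right. The normal reference carries a large share of the excess. The simulations cover binary outcomes measured on mothers or families, whereas time to referral, the two composite hand-washing scores and the volunteer and staff measures have other data structures. The family-error range also assumes independence, although several outcomes come from the same households; positive correlation would lower it.

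What the reply does not remove is that the article presents the three methods as interchangeable and promises Bonferroni control in the same section. At the stated number of clusters, one of those methods in its ordinary form does not keep that promise. That is a problem with the choice offered, beyond a missing detail.

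**Conclusion.** The point holds as a conditional one. If GEE is used with an uncorrected sandwich variance and normal critical values, a binary patient-level primary outcome tested at 0.05/6 would have an error rate of roughly 2.3 to 3.6 % instead of 0.83 %, and the Bonferroni correction would not hold the 5 % family error. The main driver, 16 clusters, is stated in the article. The multiple stayed between 2.6 and 4.3 across the 42 scenarios of assumed ICC, prevalence, cell size and model form. The divisor of 6 and two-sided testing are readings of the text. A mixed model with about the right correlation structure would not show this degree of inflation. If an existing analysis plan already selects such a model with small-sample degrees of freedom, or a corrected GEE, the point is met.

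**What to change.** Name one primary model before the analysis, and state with it:

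- for GEE, a small-sample corrected variance (Mancl-DeRouen or Kauermann-Carroll) with a t reference on clusters minus 2, that is 16 − 2 = 14 df. Of these two, Mancl-DeRouen is the one checked above;
- for a random effect or multilevel model, a small-sample degrees-of-freedom method such as Kenward-Roger;
- or, as an alternative to both, a permutation test that re-draws the centre start dates under the stratified scheme actually used.

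State the Bonferroni divisor in the same place. The cost is a sentence or two and no extra data. Confidence intervals become somewhat wider, and the Mancl-DeRouen version can be slightly conservative.

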## Background

While global estimates of newborn mortality have been declining, it remains an important public health problem in low income countries, particularly in settings where under five-year-old and maternal mortality rates have decreased more rapidly [1, 2]. It is estimated that up to 40 % of global under five-year-old mortality occurs in the newborn period (during the first 28 days after birth) [3]. In Cambodia, maternal and under five-year-old mortality rates have been significantly reduced over the last 10 years, falling from 472 per 100,000 live births in 2005 to 206 per 100,000 live births in 2010, and 83 per 1,000 live births in 2005 to 54 per 1,000 live births in 2010, respectively. Newborn mortality, however, has been more difficult to address at 28 per 1,000 live births and 27 per 1,000 live births in 2005 and 2010 [4, 5].

In order to address the continued newborn mortality burden, the Cambodian Ministry of Health (MoH), under the guidance of the Prime Minister, resolved to redouble efforts to achieve significant progress in reducing newborn mortality at its Annual Congress in 2011. Attendees at the Annual Health Congress, including the United States Agency for International Development (USAID), the National Reproductive Health Program, and key non-governmental organizations (NGOs) and United Nations partners were called upon and agreed to work with the MoH in reducing high newborn and child mortality rates in Cambodia. As yet, however, there has been no agreed national strategy on how best to achieve the called-for reductions.

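### Minor: the month-by-month mortality comparison, if run as separate contrasts, has almost no power in any month; mortality should be tied to one pooled, month-adjusted estimate

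*Protocol article*

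**What the plan says.** Under Analysis plan, the article first announces descriptive statistics by time and group, then two-group "comparison analysis at each time point, across all time points and within each cluster will be performed". It next says that stepped-wedge data will be analysed with allowance for within-cluster correlation, by a random effect model, a multilevel model or generalized estimating equations. Mortality is named once, in the following sentence: "Based on each month of the study, we will compare the neonatal mortality rate in those centers that have not yet received the intervention" with that in centers that have. The section sets a 5 % level for the study hypothesis and applies Bonferroni to the primary outcomes only.

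Mortality is listed under Exploratory outcomes, with a warning that power may be insufficient. It is nevertheless the outcome behind the sample size, whose stated aim is "to detect a 20 % reduction in neonatal mortality". For that calculation the article assumes a starting rate of at most 40 per 1,000 in the province, power of 80 %, alpha of 5 % and 10 % lost to follow-up. Under Trial design, "The study will enroll a target sample size of 1,957 recently delivered women"; the same section fixes the steps: "On the hypothesis that 16 health centers are recruited, one health center will be assigned to start each month".

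**The concern.** A stepped-wedge trial gains its information by combining within-month contrasts over all months. One month taken alone compares a few dozen women with a few dozen others on an event that occurs in 3-4 % of births, and in the first and last mixed months one side is a single health center. Such contrasts cannot show a 20 % reduction, and each extra test is another chance of a spurious significant month. Because Bonferroni is confined to the primary outcomes, nothing in the article would restrain the reading of such a month. This matters somewhat beyond an ordinary exploratory outcome, because the dissemination section foresees publications on the impact on neonatal mortality and policy change to follow.

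**Working it through.** **Inputs.** 1,957 women; 16 centers, one starting per month on 16 start dates (Trial design). Baseline 40 per 1,000 and a 20 % reduction (Sample size section). The Background gives national rates "at 28 per 1,000 live births and 27 per 1,000 live births in 2005 and 2010"; I use 27 as the lower case. At least 320 births per month over 17 months (Sample size section); 320 × 17 = 5,440. Assumptions of mine: even enrolment over time, two-sided 5 % tests, no clustering in the monthly tests (which flatters them).

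**The plan's own figure.** Two proportions, 0.040 v 0.032, pooled rate 0.036, n per group:
[1.960·√(2·0.036·0.964) + 0.842·√(0.040·0.960 + 0.032·0.968)]² / 0.008² ≈ 8,511.
That is 17,022 in total, or 18,914 after dividing by 0.9 for loss, before any clustering. The stated 1,957 does not reproduce. That is a separate and larger matter, but it explains why every mortality analysis below is weak.

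**Mixed months.** With one center starting per month, both conditions coexist while 1 to 15 of the 16 centers have started: 15 months.

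**Deaths per month, both groups together** (women per month × rate):

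| Spread of 1,957 | Women/month | All at 40 | All at 27 | All at 27, reduced to 21.6 |
|---|---|---|---|---|
| 16 months | 122 | 4.9 | 3.3 | 2.6 |
| 17 months | 115 | 4.6 | 3.1 | 2.5 |
| 22 months (16 + 6) | 89 | 3.6 | 2.4 | 1.9 |

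So about two to five. At 320 births: 320 × 0.0216 = 6.9 to 320 × 0.040 = 12.8.

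**Power of one month.** Power = Σ Bin(a; n₀, p)·Bin(b; n₁, 0.8p) over all (a, b) for which Fisher's two-sided p ≤ 0.05. Size is the same sum with p on both sides. I enumerated all 15 splits.

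| Women/month | Baseline per 1,000 | Power, range over 15 splits | Size, range |
|---|---|---|---|
| 115 | 40 | 1.0-3.6 % | 1.2-2.4 % |
| 115 | 27 | 0.6-2.7 % | 0.5-2.0 % |
| 122 | 40 | 0.7-3.6 % | 0.7-2.3 % |
| 122 | 27 | 0.2-2.8 % | 0.2-2.0 % |
| 320 | 40 | 1.4-5.5 % | 2.3-3.6 % |
| 320 | 27 | 1.3-5.0 % | 1.8-3.5 % |

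A balanced month shows why. With 58 v 58 women the expected deaths are 58 × 0.040 = 2.3 and 58 × 0.032 = 1.9. With no deaths on one side, 5 v 0 gives p = 0.057, so at least 6 v 0 (p = 0.027) is needed. Power there is 0.6 % at 40 per 1,000 and 0.2 % at 27. With one started center (about 7 v 108 women, 40 per 1,000) power is 1.1 % against a size of 1.8 %: a reduction makes rejection less likely than no effect does.

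**Chance of at least one false-positive month.** 1 − Π(1 − sizeₜ) over 15 months: 26 % (40 per 1,000) and 20 % (27) at 115 women; 37 % and 34 % at 320. Spreading 1,957 over 22 months lowers it to 21 % and 15 %. This treats months as independent and each as tested at 5 %.

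**Pooled analysis, month as fixed effect, ICC 0.** Hussey-Hughes variance = p̄(1 − p̄) / [n·Σ t(16 − t)/16], where n is women per center-month over 16 × 17 cells and Σ for t = 1 to 15 is 680/16 = 42.5.
- 1,761 evaluable (0.9 × 1,957): n = 6.474. At 40 per 1,000, SE = √(0.0347/275.2) = 0.0112, z = 0.008/0.0112 = 0.71, power = Φ(0.71 − 1.96) ≈ 11 %. At 27, about 8 %.
- 4,896 evaluable (0.9 × 5,440): n = 18. Power is about 22 % at 40 and 16 % at 27.

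The monthly rows make no deduction for loss. Without it the pooled figures at 1,957 are 11.3 % and 8.9 %, so the contrast does not turn on that. A positive ICC lowers them: at ICC 0.2 with 1,761, to 7.6 % and 6.3 %.

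**The case against.** The strongest reply is that the remedy is largely in the plan already. The section includes a comparison over all time points and a clustered model, and the model sentence stands directly before the mortality sentence. The mortality sentence names no test and no p-value; it can be read as describing the within-month comparison that a stepped-wedge model combines. This stands in part. A reader might infer that mortality will be reported only as a series of monthly p-values. The article does not support that. What remains is that the model is not tied to mortality, no month term is named, and the plan for comparisons at each time point leaves separate contrasts open.

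A reader might also infer 15 tests at a true 5 %, hence a 54 % chance of a false positive (1 − 0.95¹⁵). That does not follow either. The 5 % level is stated for the study hypothesis, and the Hypotheses section concerns knowledge, case detection, referral and causes of sepsis. With so few deaths an exact test also runs well below 5 %, which gives the 20-37 % above.

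That no rate ratio with a confidence interval is stated is not a fault: an article may leave effect measures to the full plan. Limiting Bonferroni to primary outcomes is ordinary practice, and the weak power for mortality is disclosed. Finally, pooling does not rescue the outcome, because low power comes mainly from the sample size. All of this stands and holds the point to a clarification.

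**Conclusion.** The point holds as a minor one. If the mortality sentence is carried out as separate monthly contrasts, each has about 0.2-4 % power for the 20 % reduction at target enrolment and 1-5.5 % at 320 births per month. That is near the test's own size, so a significant month would say little about the intervention. If all 15 were tested, a false-positive month would arise with probability about 20-26 % (34-37 % at 320 per month).

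The conclusion does not depend on which enrolment figure or baseline rate is used. It does depend on reading the sentence as separate contrasts, which the wording allows but does not compel. The false-positive figures further assume exact tests at 5 %, independence between months and, for 1,957 women, a 17-month even spread. The low power is the firmer part.

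**What to change.** Replace the monthly sentence with one stating that neonatal mortality is analysed once, by the cluster model already planned, over all months together with month as a fixed effect, giving one effect estimate with its 95 % confidence interval. Show monthly rates by condition in a table or figure, without tests. Add that this is estimation for an exploratory outcome and not a test able to detect a 20 % reduction, since pooled power is only about 8-11 % (1,761 evaluable) or 16-22 % (4,896) even at ICC 0.

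The cost is a sentence or two in the analysis plan. It needs no change to data collection, randomization or enrolment, and is less work than 15 monthly comparisons.
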